#### Subject discontinuation/withdrawal

Subjects may voluntarily discontinue participation in the study at any time. If a subject is removed from the study, the clinical and laboratory evaluations that would have been performed at the end of the study should be obtained. If a subject is removed because of an adverse event, they should remain under medical observation as long as deemed appropriate by the treating physician.

#### Follow-up evaluation

No study-specific follow-up visits are required for study participants, clinic visits will be standard of care.

### Statistical considerations

#### Sample size

Simon’s two-stage design will be used to determine the proportion of patients with treatment changes following EBUS/EUS-B staging. The null hypothesis that the true response rate is 10% will be tested against a one-sided alternative. In the first stage, 10 patients will be accrued. If there are 1 or fewer responses (treatment changes) in these 10 patients, the study will be stopped. Otherwise, 19 additional patients will be accrued for a total of 29. The null hypothesis will be rejected if 6 or more responses (treatment changes) are observed in 29 patients. This design yields an alpha of 0.05 and power of 80% when/if the true treatment change rate is 30%.

#### Statistical analysis

Descriptive statistics will be generated for baseline patient, tumour and treatment characteristics for all patients enrolled in either the first stage (*n* = 10) or second stage (*n* = 19) of the Simon’s two-stage design. The primary endpoint of this study will be to determine the proportion of patients with changes to treatment intent and/or plan, which will be reported with a 95% confidence interval and compared against the null hypothesis of no changes (0%) using the binomial proportion test. The secondary endpoints of this study will include determining the proportion of patients with occult mediastinal metastasis, which will also be reported with a 95% confidence interval. The sensitivity, specificity and concordance (using univariable logistic regression) measuring the association between radiologic staging of hilar/mediastinal lymph nodes (predictor variable) and changes in treatment intent and/or plan (dependent variable) will be calculated. The total number of lymph nodes sampled per procedure and proportion sampled for each nodal station will be calculated for each patient. The proportion of patients with complications of endoscopic procedure will also be reported. All statistical analyses will be performed using SAS version 9.4 software (SAS Institute, Cary, NC, USA) with two-sided statistical testing at the 0.05 significance level.

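### The primary endpoint is tested against a null of 0%, although the trial was sized against a null of 10%; one treatment change rejects 0%, and the stated alpha and power do not describe that test

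*Protocol article*

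**What the plan says.** The Sample size section of the protocol article gives a complete decision rule. It states: "The null hypothesis that the true response rate is 10% will be tested against a one-sided alternative". Stage 1 enrols 10 patients, and "If there are 1 or fewer responses (treatment changes) in these 10 patients, the study will be stopped". If the trial continues, 19 more patients bring the total to 29, and "The null hypothesis will be rejected if 6 or more responses (treatment changes) are observed in 29 patients". The section claims an alpha of 0.05, and 80% power at a true change rate of 30%.

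The Statistical analysis section takes up the same primary endpoint. The proportion of patients with a change in treatment intent or plan is to be reported with a 95% confidence interval and "compared against the null hypothesis of no changes (0%) using the binomial proportion test". The section ends by making all statistical testing two-sided at the 0.05 level.

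The article therefore gives two null values (10% and 0%) and two directions (one-sided and two-sided) for one primary endpoint. It does not say which test decides.

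**The concern.** A null of 0% is degenerate for a proportion. If the true rate is 0, a change is impossible, so a single change disproves the null and further patients add nothing. The test answers only whether any patient's plan changed. The design asks whether the change rate exceeds 10%, and 10% is also the benchmark in the Abstract, the opening of Methods/design and the Discussion; 0% appears only in the analysis section.

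An analyst who follows the Statistical analysis section would report a significant primary result for data on which the Sample size section does not reject its null. The article says the results will inform phase II trials, so a p-value against 0% could be read as evidence that endoscopic staging changes management often enough to matter.

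**Working it through.** **Inputs.** From Sample size: null 10%, alternative 30%, one-sided; stage 1 of 10 patients, stop at 1 or fewer changes; total 29, reject at 6 or more; stated alpha 0.05 and power 80%. From Statistical analysis: null 0%, binomial test, two-sided 0.05.

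**1. Reproduce the stated design.** With X1 the changes in the first 10 patients and X2 those in the next 19,

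P(reject | p) = Σ over x = 2 to 10 of P(X1 = x) × P(X2 ≥ max(0, 6 − x)).

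At p = 0.10:

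| x | P(X1 = x) | X2 needed | P(X2 at least that) | Product |
|---|---|---|---|---|
| 2 | 0.1937 | 4 | 0.1150 | 0.0223 |
| 3 | 0.0574 | 3 | 0.2946 | 0.0169 |
| 4 | 0.0112 | 2 | 0.5797 | 0.0065 |
| 5 | 0.0015 | 1 | 0.8649 | 0.0013 |
| 6 or more | 0.0001 | 0 | 1 | 0.0001 |

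The sum is 0.0471. The same sum at p = 0.30 is 0.8051. Both agree with the stated alpha of 0.05 and power of 80%; 0.0471 falls below 0.05 only because the counts are discrete. The Sample size section is correct for its own rule.

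**2. The test against 0%.** P(X ≥ 1 | p = 0) = 0 for any n, and the null standard error is √(0 × 1/n) = 0. One change rejects. A trial with 0 of 10 stops without rejecting, so over the whole two-stage trial the chance of rejecting 0% is P(X1 ≥ 1) = 1 − (1 − p)^10. At p = 0.10 this is 1 − 0.9^10 = 1 − 0.3487 = 0.6513.

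**3. How often the two sections disagree.** Every trial that meets the 6-of-29 rule also rejects 0%, so the disagreement is the difference between the two probabilities.

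| True rate | Rejects 0% | Meets the two-stage rule | Opposite conclusions |
|---|---|---|---|
| 5% | 40.1% | 0.2% | 39.9% |
| 10% | 65.1% | 4.7% | 60.4% |
| 30% | 97.2% | 80.5% | 16.7% |

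At 10% the disagreement has two parts:
- The trial stops at exactly 1 of 10: 10 × 0.1 × 0.9^9 = 38.7%.
- The trial completes stage 2 with 2 to 5 of 29: P(X1 ≥ 2) − P(reject) = 0.2639 − 0.0471 = 21.7%.

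Any trial that enters stage 2 already has at least 2 changes, so the 0% test is settled before the last 19 patients are enrolled.

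**4. Is it enough to replace 0% with 10%?** No. An ordinary exact binomial test of 10% that ignores the interim stop gives a one-sided p of 0.0637 at 6 of 29, and 0.0216 at 7 of 29. It would need 7 changes, against the stated cut-off of 6. The one-sided p-value under the two-stage sampling distribution is 0.0471 at 6 of 29, which matches the rule. The single-stage value is larger because it counts outcomes that the stopping rule excludes (1 or fewer changes in the first 10, yet 6 or more in 29). Doubling 0.0637 for a two-sided test gives 0.127, so the two-sided wording also conflicts with the cut-off.

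**The case against.** The best defence is that the Sample size section states a full decision rule, nothing revokes it, and the analysis section still refers to the Simon design. On that reading the stated alpha and power hold, and the 0% comparison is a harmless extra beside the confidence interval. The first part stands: alpha and power are right for the two-stage rule, and the fault lies only in the test named for the analysis. The second part does not. The analysis section names the primary endpoint, a null and a test, which makes the comparison a hypothesis test rather than a description, and nothing ranks it below the design rule.

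Three further points limit how the numbers should be read:

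- The 65.1% and 4.7% are not two type I error rates. The 0% test has a type I error of zero for its own null; 65.1% is how often it rejects when the true rate is 10%. The defect is that the test does not address the design's question.
- It would be too strong to say that nearly every trial becomes significant. At a true rate of 10%, 34.9% of trials have no change in the first 10 patients and do not reject 0%; at 5% it is 59.9%.
- The article does not say outright that the primary test is run after a stop at stage 1. The completed trial with 2 to 5 changes in 29 needs no such reading and is the firmer example.

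Enrolment, stopping and data collection are unaffected, and the confidence interval would let a careful reader compare the result with 10%. That limits the harm but leaves the primary test undefined.

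**Conclusion.** The concern holds and must be fixed. The article gives incompatible nulls for its primary endpoint, and the one in the analysis section is degenerate. At a true rate of 10% the two sections reach opposite conclusions in 60.4% of trials if the 0% test is also applied after a stop at stage 1, and in 21.7% if only completed trials are counted. These figures assume independent patients with a common change rate, exactly 10 and 29 evaluable patients, and adherence to the stopping rule. The contradiction itself rests on no assumption.

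**What to change.** In Statistical analysis:

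1. Remove the comparison with 0%. State that the primary hypothesis is H0: p ≤ 10% against p > 10%, decided by the two-stage rule already in Sample size (stop at 1 or fewer of 10; reject at 6 or more of 29).
2. State that any p-value for this endpoint is one-sided and computed under the two-stage sampling distribution, so that it agrees with the cut-off of 6. An ordinary binomial test of 10% would not.
3. Limit the two-sided 0.05 sentence to analyses other than the primary test.

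The 95% confidence interval can stay as the estimate. The cost is two or three sentences. The sample size, alpha (0.0471) and power (0.8051) stay as they are, and no further patients or data are needed.

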**Methods:**

This is a multi-centre, prospective, cohort study with two-stage design. In the first stage, 10 patients with oligometastatic NSCLC (lung tumour ± hilar/mediastinal lymphadenopathy) with up to 5 synchronous metastases will be enrolled An additional 19 patients will be enrolled in the second stage if rate of treatment change is greater than 10% in the first stage. Patients will be subject to EBUS or combined modality EBUS/EUS-B to assess bilateral lymph node stations using a N3 to N2 to N1 progression. Primary endpoint is defined as the rate of change to treatment plan including change from SABR to conventional dose radiation, change in mediastinal radiation field, and change from curative to palliative intent treatment.

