## Background

Historically, the treatment of advanced non-small cell lung cancer (NSCLC) has focused on minimizing symptoms, and prolonging life [1]. The oligometastatic paradigm of cancer argues that distant disease is not widespread, but rather constrained by host anatomical and physiological factors, into one or a few distant organs [2, 3]. Recently, a phase II study evaluating aggressive treatment with stereotactic ablative radiotherapy (SABR) of oligometastatic disease of any cell type, has been associated with an improvement in overall survival compared to standard of care [4]. Phase III studies are currently enrolling patients to validate the results of this promising study.

Regional or distant metastasis in NSCLC are non-invasively assessed by computed tomography (CT), positron emission tomography (PET), integrated PET/CT, magnetic resonance imaging (MRI) and radionucleotide bone scans [5]. PET/CT has been particularly useful in detecting occult metastases and avoiding futile surgical resection [6]. However, a large meta-analysis of integrated PET/CT for mediastinal nodal involvement in NSCLC reported sensitivity and specificity of only 81 and 79%, respectively [7]. Despite widespread reliance on PET/CT, mediastinal staging still identifies occult nodal disease in up to 20% of NSCLC patients who are operative candidates [8, 9].

Endobronchial ultrasound and transbronchial needle aspiration (EBUS-TBNA) for invasive mediastinal staging is a powerful and minimally invasive tool used to stage and diagnose thoracic malignancies [5, 8–10]. When EBUS is combined with endoscopic ultrasound (EUS) using the same bronchoscope (EUS-B), the diagnostic sensitivity and negative predictive value increase to 84 and 97%, respectively [11].

Treatment paradigms in the past did not justify invasive mediastinal staging for patients with advanced disease, therefore the presence of occult mediastinal metastasis has never been elucidated. However, if a curative approach for oligometastatic disease is being explored, invasive mediastinal staging may inform treatment planning and guide prognosis.

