#### Endoscopic procedure

All procedures will be performed by one of the study investigators. Procedures will be performed in an endoscopy setting with moderate conscious sedation, without the use of general anesthesia. EBUS-TBNA will be used to assess bilateral lymph nodal stations in the following areas: 2, 3P, 4, 5, 7, 10, and 11. EBUS may be combined with EUS-B to enhance accessibility to stations 4 L, 7, 5, 8, and 9. The use of EUS-B is not mandatory. EBUS will always be performed initially to reduce risk of airway contamination. Nodal assessment will be done systematically using a N3 to N2 to N1 progression, and any lymph node > 5 mm in short axis or with malignant features (one or more of: round shape, hypoechoic, loss of central hilar structures, central necrosis) will be sampled a minimum of 3 times. A new needle will be obtained upon stage migration to avoid contamination. Rapid onsite cytological evaluation (ROSE) will not be used for assessing samples. All specimens will be placed into formalin fixative followed by a needle-rinse into cytolyte and formally reviewed by a cytopathologist.

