#### Radiation therapy

Radiation treatment intent and dosage will be initially planned based on clinical imaging, prescribed by the treating radiation oncologist and/or based on discussion at a multi-disciplinary cancer conference. Following endoscopic staging, any changes to radiation treatment intent or dosage will be recorded.

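### Sensitivity and specificity of radiologic nodal staging are set against treatment change, so the written analysis does not answer the diagnostic-accuracy secondary endpoint

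*Protocol article*

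**What the plan says.** The Secondary endpoints list in the protocol article includes the accuracy (sensitivity and specificity) of imaging in staging the hilar and mediastinal nodes. Background uses these two terms in their ordinary sense: a meta-analysis of integrated PET/CT, judged against mediastinal nodal involvement, "reported sensitivity and specificity of only 81 and 79%, respectively".

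Statistical analysis has one sentence on the endpoint. It begins "The sensitivity, specificity and concordance (using univariable logistic regression) measuring the association between radiologic staging" and names its variables as "radiologic staging of hilar/mediastinal lymph nodes (predictor variable) and changes in treatment intent and/or plan (dependent variable) will be calculated".

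Three other sections bear on this:

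- **Treatment change** is a management outcome. The Abstract lists "change from SABR to conventional dose radiation", an altered mediastinal field, and a move from curative to palliative intent. Primary endpoints lists the same three.
- **The starting plan** already contains the imaging result. Radiation therapy says: "Radiation treatment intent and dosage will be initially planned based on clinical imaging". Changes are recorded after endoscopy.
- **Nodal pathology** is obtained. Under Endoscopic procedure, all specimens are "formally reviewed by a cytopathologist".

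No section names cytology, or any other nodal finding, as the reference for sensitivity and specificity.

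**The concern.** Sensitivity is the proportion of patients with the target condition whom the test calls positive. Here the target condition is nodal disease, but the outcome in the analysis is a decision about treatment.

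The two differ in a systematic way. The first plan is built on the scan, so a scan that endoscopy confirms gives little reason to change it, and a scan that endoscopy contradicts gives more. In imaging-positive patients the scoring therefore tends to run backwards: a correct positive tends to be scored as a false positive, and a wrong positive that alters treatment is scored as a true positive. The concordance statistic from the logistic model likewise describes how well imaging stage predicts a change of plan. It does not describe agreement with pathology.

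At stake is one named secondary endpoint. Its results would carry the labels sensitivity and specificity, and readers would naturally set them beside 81% and 79%, although they answer a different question.

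**Working it through.** **The plan's own figures.** The article states no figure for this analysis. Its only computed figures belong to the two-stage design (10 then 19 patients, stop at 1 or fewer, reject at 6 or more of 29, 10% versus 30%). Exact binomial calculation gives alpha 0.0471 and power 0.805, in line with the stated 0.05 and 80%. That design does not depend on this point.

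**Inputs.** From Background: Se = 0.81 and Sp = 0.79 for PET/CT against nodal involvement. Assumed, because the documents give no values: nodal prevalence π of 20%, 40% and 60%; cytology correct; treatment changed exactly when imaging and cytology disagree at patient level.

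**Formulas.** As proportions of all patients:

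- TP = π·Se, FN = π·(1 − Se), FP = (1 − π)·(1 − Sp), TN = (1 − π)·Sp
- Changed = FP + FN; unchanged = TP + TN
- Sensitivity for change = imaging-positive among changed = FP/(FP + FN)
- Specificity for change = imaging-negative among unchanged = TN/(TN + TP)

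**Results.**

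| π | TP | FN | FP | TN | Sensitivity for change | Specificity for change |
|---|---|---|---|---|---|---|
| 20% | 0.162 | 0.038 | 0.168 | 0.632 | 0.168/0.206 = 82% | 0.632/0.794 = 80% |
| 40% | 0.324 | 0.076 | 0.126 | 0.474 | 0.126/0.202 = 62% | 0.474/0.798 = 59% |
| 60% | 0.486 | 0.114 | 0.084 | 0.316 | 0.084/0.198 = 42% | 0.316/0.802 = 39% |

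The scan is the same in every row, with true accuracy 81%/79%. The near match at 20% is a coincidence, because the cells that enter the two fractions are not the ones that define accuracy.

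**Whole patients.** Take 29 patients with TP 9, FN 2, FP 4, TN 14 (assumed counts). Against cytology, sensitivity is 9/11 = 81.8% and specificity 14/18 = 77.8%. Against treatment change under the same rule, they become 4/6 = 66.7% and 14/23 = 60.9%.

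**Other change rules.**

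- *Change in all FN, half of FP and 10% of TP.* This allows some correctly node-positive patients a field change. At π = 40%, changed = 0.076 + 0.063 + 0.0324 = 0.1714. Sensitivity for change is (0.063 + 0.0324)/0.1714 = 56% and specificity 0.474/(1 − 0.1714) = 57%. At π = 20% they are 73% and 73%.
- *Change only in imaging-negative, cytology-positive patients.* Sensitivity for change is 0% at every prevalence; specificity is 66% at π = 20% and 51% at π = 40%.

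The values move with the rule and the prevalence while the scan's accuracy stays fixed.

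**The case against.** **Another reading of the sentence.** The clause about association, with its regression vocabulary, could attach to concordance alone. Sensitivity and specificity would then have no stated reference, which a condensed article may leave to the full protocol. This is grammatically possible but less natural: one predictor and one outcome follow a list of three measures, and treatment change is the only outcome named. Even on this reading the sentence needs clarifying.

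**The figures are hypothetical.** This stands. Prevalences of 20%, 40% and 60% and the change rules are not in the documents. The occult-disease figure in Background (up to 20%) refers to operative candidates and is not total nodal prevalence. The 81%/79% is for PET/CT, while the Inclusion criteria also allow CT with bone scan. The table shows that the measures drift and does not predict the trial's results.

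**Stronger claims that a reader might infer.** One is that a correct positive scan always counts as a false positive. Another is that a perfect scan would leave sensitivity undefined. Both hold only if treatment changes exactly on patient-level disagreement. The documents do not say that. A change of mediastinal field counts as a treatment change, so a correctly node-positive patient in whom endoscopy finds a further station can have one. The 0% result has the same limit.

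**Cytology is not a perfect reference.** This also stands. Background cites 84% sensitivity for the combined procedure, EUS-B is optional, and only nodes above 5 mm or with malignant features are sampled. That calls for a stated limitation. It does not make treatment change a measure of nodal status.

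**Conclusion.** The analysis is wrong as written and should be corrected. On its natural reading, Statistical analysis computes sensitivity and specificity against a management outcome, while the endpoint asks about nodes. That conclusion rests on the wording and on the imaging-based initial plan, and on no particular prevalence. That cytology is the proper reference is an inference from the endpoint's wording, from the usage in Background and from the specimens the study obtains; the endpoint does not name it.

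The size is illustrative. With true accuracy of 81%/79%, correct cytology and change exactly on disagreement, the reported pair would run from 82%/80% to 42%/39% as assumed prevalence goes from 20% to 60%.

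A reader might infer that the trial's main conclusion is compromised. The documents do not support that: the primary endpoint, the stage-one stopping rule and the final rejection rule do not use this analysis. The fault is confined to one descriptive secondary endpoint.

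**What to change.** Reword the sentence in Statistical analysis as two separate analyses:

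1. **Diagnostic accuracy.** Sensitivity and specificity of radiologic hilar/mediastinal staging (positive or negative), per patient, with EBUS/EUS-B cytology as the reference and exact 95% confidence intervals. State how nodes or stations that were not sampled are classified. Note that cytology is an imperfect reference, citing the 84% already in Background.
2. **Association with treatment change.** The univariable logistic model of treatment change on radiologic stage, with its concordance statistic, labelled exploratory and not described as sensitivity or specificity.

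Kappa for N category, per-station tables and a split by PET/CT versus CT staging are optional. With at most 29 patients a split would be very imprecise.

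The cost is a rewording. Staging imaging is an entry requirement and cytology of sampled nodes is part of the procedure, so the per-patient analysis needs no new procedure. The article does not say whether imaging results are recorded by station; that should be checked before any per-station analysis is promised.

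### The primary test is designed as one-sided, but the analysis section puts every test at two-sided 0.05; once that section's null is aligned to 10%, the two rules disagree at 6/29

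*Protocol article*

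**What the plan says.** The Sample size section of the protocol article gives a complete decision rule.

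- Hypothesis and direction: "The null hypothesis that the true response rate is 10% will be tested against a one-sided alternative".
- First stage: "In the first stage, 10 patients will be accrued", and "If there are 1 or fewer responses (treatment changes) in these 10 patients, the study will be stopped".
- Second stage: "Otherwise, 19 additional patients will be accrued for a total of 29".
- Final rule: "The null hypothesis will be rejected if 6 or more responses (treatment changes) are observed in 29 patients".
- Claimed properties: "This design yields an alpha of 0.05 and power of 80% when/if the true treatment change rate is 30" per cent.

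The Statistical analysis section describes the primary analysis differently. It reports the proportion with a 95% confidence interval and compares it with a null of 0% by a binomial proportion test. Its last sentence places all analyses under SAS 9.4 "with two-sided statistical testing at the 0.05 significance level". Nothing there exempts the primary endpoint or refers back to the two-stage rule.

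**The concern.** The trial has one confirmatory decision, and two neighbouring sections give it different directions. A rule built so that about 5% of null trials reject in the upper tail is not a two-sided 5% test, which allows 2.5% in that tail.

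An obvious correction to the analysis section is to replace 0% by 10%, the rate in the Sample size section. If only that is changed, the section's test would give p above 0.05 at 6/29, a count the Sample size section calls a rejection. The critical count could then be argued to be six or seven after the data are known. If seven were adopted, the trial would no longer have its stated 80% power.

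**Working it through.** **Inputs (Sample size section).** Null rate 0.10; alternative 0.30; first stage of 10, continuing with two or more changes; 19 further patients; reject at six or more of 29. From the Statistical analysis section: two-sided, 0.05, null 0%, 95% interval.

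**1. Reproduce the stated alpha and power.** With cut-off r, P(reject | p) = Σ over x = 2 to 10 of Bin(x; 10, p) × P(Bin(19, p) ≥ r − x).

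For r = 6 and p = 0.10, the terms for x = 2, 3, 4 and 5 are:

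- 0.19371 × 0.11500 = 0.02228
- 0.05740 × 0.29456 = 0.01691
- 0.01116 × 0.57974 = 0.00647
- 0.00149 × 0.86491 = 0.00129

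The terms from x = 6 upward add about 0.00015, giving **0.0471**. The same sum at p = 0.30 gives **0.8051**. The plan's 0.05 and 80% are therefore reproduced, as one-sided figures. The upper tail of 0.0471 exceeds 0.025, so this rule is not a two-sided 5% test.

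**2. The analysis section as written (null 0%).** If the true rate were 0, the probability of any change would be 0. One change in 29 already gives p = 0, and so does 6/29. With this null, sidedness has no effect on the result at 6/29.

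**3. The analysis section with the null aligned to 10%.** The observed proportion is 6/29 = 0.2069, and the standard error under the null is √(0.10 × 0.90 / 29) = 0.0557. So z = (0.2069 − 0.10)/0.0557 = 1.919. The exact fixed-sample upper tail is P(Bin(29, 0.10) ≥ 6) = 0.0637.

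| Test of 6/29 against 10% | One-sided p | Two-sided p |
|---|---|---|
| Normal approximation | 0.0275 | 0.055 |
| Exact, fixed sample, minimum likelihood | 0.064 | 0.064 |
| Exact, fixed sample, doubled tail | 0.064 | 0.127 |
| Two-stage distribution (doubled for two-sided) | 0.047 | 0.094 |

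In the minimum-likelihood row the lower tail adds nothing, because zero changes (probability 0.0471) is more likely under 10% than six changes (0.0421). Every two-sided entry is above 0.05.

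**4. How much is due to sidedness?** The one-sided exact fixed-sample p is also above 0.05. It counts outcomes with at most one change in the first 10 but six or more overall, which the stopping rule makes impossible. Those outcomes carry 0.0637 − 0.0471 = 0.0166. So there are two sources of mismatch: direction, and a test that ignores the first-stage stop. Direction alone still matters, since the doubled two-stage p is 0.094.

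**5. A cut-off of seven.** At 7/29 the two-sided exact p is 0.022 (minimum likelihood) or 0.043 (doubled tail). With r = 7, the sum in step 1 gives alpha **0.0177** and power **0.7389**.

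**6. How often it would matter.** The chance of passing the first stage and ending on exactly six is 0.8051 − 0.7389 = 0.066 at a true rate of 30%. The same calculation gives 0.125 at 20%.

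**7. The interval.** At 6/29 the ordinary 95% interval is 8.0% to 39.7% (Clopper-Pearson), 9.8% to 38.4% (Wilson) or 5.9% to 35.4% (Wald). All include 10%. An ordinary 90% Clopper-Pearson interval, 9.4% to 36.8%, also includes it, so changing the level without allowing for the two stages would not be enough.

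**The case against.** The strongest reply is that the Sample size section gives an explicit count rule, and a specific rule normally takes precedence over a general sentence on software and significance level that closes a paragraph also covering secondary endpoints. A sensible analyst would apply the count. This has force and limits the practical harm. It does not remove the contradiction, because the same paragraph names a separate test for the primary endpoint and then puts all analyses under two-sided 0.05.

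A second reply concerns a stronger reading. A reader might infer that the document, as it stands, calls 6/29 a success in one section and non-significant in the other. It does not. The analysis section tests against 0%, and against 0% both 6/29 and 1/29 reject. On the nulls actually printed, choosing a side does not change the result at 6/29. The boundary conflict depends on carrying the 10% null into the analysis section.

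A third reply is that sidedness should not take all the blame, because an exact fixed-sample test at 6/29 misses 0.05 even one-sided. That is correct, and for this reason changing the one word would not be a sufficient repair. The article also does not say whether the binomial test is exact or asymptotic. Direction alone decides the result for the normal approximation (0.0275 against 0.055) and for the two-stage p-value (0.047 against 0.094).

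**Conclusion.** The contradiction in direction is real. The primary test is "tested against a one-sided alternative" in one section and falls under a blanket two-sided rule in the next, and the stated alpha, power and cut-off are correct only as one-sided figures (0.047 and 0.805).

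The numerical consequence is conditional. It assumes that the null in the analysis section is aligned to 10% and that the two-sided sentence stays. Then 6/29 gives a two-sided p between 0.055 and 0.127, and adopting seven as the cut-off gives alpha 0.018 and power 0.739. Part of the gap comes from a fixed-sample test that ignores the first-stage stop, not from sidedness.

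The effect is confined to a final count of exactly six: about 6.6% of trials at a true rate of 30% and 12.5% at 20%. This is a clarification to settle before analysis; the two-stage design itself is sound. Correcting the null alone would leave the conflict in place.

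**What to change.** In the Statistical analysis section:

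1. State that the primary endpoint is tested against 10%, one-sided at 0.05, by the two-stage rule (six or more of 29), with the p-value from the two-stage distribution (0.047 at 6/29). This replaces the comparison with 0%.
2. Limit two-sided 0.05 testing to the secondary analyses.
3. Pair the decision with an interval that agrees with it, such as a 90% two-sided or a one-sided 95% interval that accounts for the two stages. If an ordinary 95% interval is also reported, label it descriptive, since it can include 10% when the rule rejects.

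The cost is a sentence or so of text and slightly more analysis work, with no change to sample size or conduct.

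If two-sided 0.05 is truly intended for the primary endpoint, the design has to be reworked. Taking one-sided 0.025 and 80% power for 10% against 30%, the design with the smallest expected size stops at one or fewer of 10 and rejects at eight or more of 38 (alpha 0.023, power 0.808). The design with the smallest maximum size stays at 29, but stops at two or fewer of 18 and rejects at seven or more (alpha 0.021, power 0.801).
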